### 3.4. Instruments

#### Questionnaires

SARC-F

The SARC-F [29] is a brief screening questionnaire consisting of five items assessing strength, assistance in walking, rising from a chair, climbing stairs, and falls. Each item is scored from 0 to 2, giving a total score range of 0 to 10. A score of ≥4 is considered indicative of sarcopenia risk and suggests the need for a more detailed musculoskeletal assessment.

EORTC QLQ-C30

The EORTC QLQ-C30 [30] is a standardized 30-item questionnaire developed to assess health-related quality of life in oncology patients. It includes functional scales (physical, emotional, cognitive, social, and role), symptom scales, and a global health/quality of life measure. Specifically, it comprises 5 functional scales (physical, role, emotional, cognitive, and social), 3 symptom scales (fatigue, pain, nausea/vomiting), 1 global health/quality of life scale, and additional individual symptom items.

Scores are linearly transformed to a 0–100 scale. For functional and global scales, higher scores indicate better functioning or quality of life. For symptom scales, higher scores indicate greater symptom severity (worse clinical status). A change of ≥10 points is generally considered clinically meaningful in many oncology contexts.

Pittsburgh Sleep Quality Index (PSQI)

The Pittsburgh Sleep Quality Index (PSQI) [31] assesses subjective sleep quality over the past month through 19 items grouped into 7 components (subjective quality, latency, duration, habitual efficiency, disturbances, use of medication, and daytime dysfunction).

Each component is scored from 0 to 3, yielding a global score ranging from 0 to 21. Higher scores indicate poorer sleep quality. A cutoff point >5 is commonly used to identify clinically relevant poor sleep quality.

It is acknowledged that the PSQI evaluates sleep quality over the previous month; repeating the assessment at discharge provides a mixed estimate of the prior period and the partial impact of hospitalization. To contextualize changes, qualitative comments on sleep specifically during the hospital stay will be recorded.

The PSQI is intended to provide a standardized assessment of baseline sleep quality and sleep-related vulnerability rather than a direct measure of short-term hospitalization-related sleep changes. Consequently, PSQI findings will be interpreted within the context of its established one-month recall period.

Handgrip Strength (HGS)

Grip strength will be assessed using the Camry EH101 hand dynamometer (Zhongshan Camry Electronic Co. Ltd., Zhongshan, China), a low-cost, portable device that has demonstrated excellent intra- and inter-instrument reliability (ICC > 0.94) and concurrent validity against the Jamar^®^ dynamometer (gold standard, Warrenville, IL, USA), with minimal systematic bias (0.5–1.4 kg) and narrow limits of agreement in adult and geriatric clinical populations, including cancer patients and healthy individuals [32].

HGS will be measured following the standardized bilateral positioning and measurement protocol from the University of Southampton [12,33]. During the assessment, participants will be seated with their back supported, shoulder in a neutral position, elbow flexed at 90°, and wrist extended between 0° and 30°. The procedure consists of performing three maximal voluntary contractions per limb, with 60 s recovery periods between efforts to prevent cumulative fatigue. For the final analysis, the highest value achieved across the three repetitions for each hand will be recorded.

Bioelectrical Impedance Analysis (BIA)

Body composition will be assessed using bioelectrical impedance analysis (BIA) with the Tanita MC-580 device (Tanita Corp., Tokyo, Japan), which employs multifrequency BIA technology like other clinically validated models from the same manufacturer and has been previously validated against Dual-Energy X-ray Absorptiometry (DXA) (Marlborough, MA, USA). These devices show high correlations (r ≈ 0.85) and technical errors of approximately 1.5–2.5% for total and segmental body fat in healthy adults and individuals with obesity [34,35]. Although this method provides acceptable accuracy for clinical and research purposes, it remains an indirect approach compared with four-compartment models, and therefore its limitations must be acknowledged, particularly in clinical populations.

Measurements will be performed following a standardized protocol. Participants will be instructed to void approximately 30 min before assessment and to rest in supine position for 15 min prior to measurement to minimize variability related to fluid redistribution. Primary electrical parameters, including resistance (R) and reactance (Xc), will be recorded, and derived indices such as phase angle, skeletal muscle mass, fat-free mass, fat mass, and total body water will be calculated. Phase angle will be considered the primary impedance-derived parameter due to its relative stability and lower sensitivity to acute fluid shifts compared to other indices derived.

To improve interpretability, hydration-related and clinical factors will be systematically recorded whenever available, including peripheral edema, ascites, recent intravenous fluid administration, fasting status, and other relevant conditions that may affect fluid distribution. Patient posture during measurement will also be documented, and all assessments will be conducted in a standardized position whenever clinically feasible.

Given the potential influence of acute fluid shifts in hospitalized oncology patients, BIA-derived body composition estimates will be interpreted as exploratory indicators rather than definitive measures of skeletal muscle mass. In this context, particular attention will be given to phase angle, as it may provide a more stable indicator of cellular integrity and nutritional status than other impedance-derived variables. However, all phase angle interpretations will be considered alongside the patient’s clinical condition and hydration status.

Body Weight, Body Mass Index, and Dietary Intake

Body weight (kg) and height (m) will be recorded at hospital admission. Body Mass Index (BMI) will be calculated as weight (kg) divided by height squared (m^2^). Body weight will be reassessed at discharge and monitored during hospitalization whenever routinely available through clinical records.

Dietary intake during hospitalization will be documented using standardized nursing and clinical nutrition records when available. Intake will be estimated as the percentage of meals consumed and categorized as adequate (>75%), moderate (50–75%), or insufficient (<50%) intake. These variables will be considered exploratory indicators of nutritional status and potential contributors to muscle deterioration.

Additional Clinical Variables

To provide a broader characterization of factors potentially influencing muscle deterioration, the following variables will be recorded whenever available from the medical record: cancer stage, reason for hospital admission, recent anticancer treatment and treatment timing, corticosteroid exposure, opioid or sedative medication use, nutritional support interventions, clinically significant infection or inflammatory complications, anemia status, mobility restrictions, and hydration-related factors, including edema, ascites, and intravenous fluid administration.

Surface Electromyography (sEMG)

Electromyographic activity was recorded using the wireless Shimmer3 system, integrated into the mDurance platform [36]. Signals were acquired at a sampling frequency of 1000 Hz, ensuring adequate temporal resolution for amplitude and frequency parameter analysis.

A band-pass filter between 10 and 500 Hz was applied to remove low-frequency components and high-frequency noise, along with a 50 Hz notch filter to suppress electrical interference. Acquisition and preprocessing parameters were kept constant across all assessments to ensure intra- and inter-subject comparability.

Skin preparation and electrode placement were performed according to SENIAM guidelines. Electrodes were positioned on the vastus lateralis, vastus medialis, and upper trapezius. The vastus lateralis and medialis were selected due to their key role in functional mobility and load transfer during activities of daily living, as well as their documented sensitivity to accelerated muscle loss in prolonged disuse and bed rest contexts [37,38,39]. The upper trapezius was chosen as an accessible postural muscle relevant during prolonged sitting, allowing evaluation of fatigue patterns distinct from those of the lower limbs [40,41].

Lower limb protocol: Three maximal voluntary contraction (MVC) attempts of 3 s each will be performed, with 2 min rest intervals between attempts. Subsequently, an isometric contraction at 65% of MVC will be maintained using biofeedback via a portable dynamometer until muscle failure, defined as the inability to maintain the target intensity (±5–10%) for more than 3–5 consecutive seconds despite visual/auditory feedback [42,43].

Upper trapezius protocol: Three MVC attempts of 3 s each will be performed, with 2 min rest intervals between attempts. This will be followed by an isometric contraction at 65% of MVC using biofeedback via a portable dynamometer until muscle failure.

Participants will perform a sustained isometric contraction at 65% of their maximal voluntary contraction (MVC). Reduction to 50% MVC will only be considered when participants are unable to safely maintain the target force level during familiarization, report excessive fatigue, pain, or discomfort, or when the research team determines that continuation at 65% MVC may compromise participant safety [43,44,45,46,47,48]. The contraction intensity selected and the reason for any modification will be documented for each assessment. To ensure isometric contractions at 65% MVC in the vastus lateralis and medialis (quadriceps) and upper trapezius during the muscle assessment protocol, the portable ActivForce 2 dynamometer (ActivForce, LLC, San Diego, CA, USA) will be used. This device provides real-time feedback via a mobile app with precise force measurements (intra- and inter-rater ICC > 0.85–0.99; concurrent validity r = 0.89–0.93 vs. microFET2 in isometric shoulder and knee movements), allowing patients to adjust intensity objectively and safely [49,50].

Participants may stop the contraction at any time if they experience pain, dyspnea, dizziness, or subjective discomfort; these events will be systematically recorded. In patients with clinical limitations, the protocol may be adjusted to 50% MVC to ensure safety without compromising the acquisition of fatigue parameters.

Surface electromyographic signals were analyzed following methodologies previously described in the literature [51]. In the time domain, the root mean square (RMS) was calculated and normalized to the value obtained during maximal voluntary contraction (%MVC), to allow intra- and inter-subject comparisons.

In the frequency domain, median frequency (MDF) and mean frequency (MNF) were estimated using the fast Fourier transform (FFT), applying consistent analysis windows throughout the signal to ensure spectral stability.

Neuromuscular fatigue indices were calculated as follows: Temporal slope of MDF during sustained contraction; Final/initial RMS ratio, as an indicator of changes in muscle activation; Time to failure, defined as the moment when the participant was no longer able to maintain the target force level; failure was considered when force decreased persistently by more than 5–10% below 65% of MVC during the isometric contraction [43,44].

During data acquisition, real-time visual inspection was performed to detect artifacts (movement, electrical interference, or loss of electrode contact), complemented by a systematic post-acquisition review to ensure the quality and consistency of the recordings prior to final analysis.

sEMG Acquisition and Signal Processing Procedures

All assessments will be performed with participants seated comfortably in a chair or hospital bed with back support. For quadriceps recordings, hips and knees will be positioned at approximately 90° flexion whenever clinically feasible, while for upper trapezius recordings, participants will remain seated with arms relaxed alongside the body. Standardized positioning will be maintained across sessions whenever possible.

Surface electromyography (sEMG) electrode placement will follow SENIAM recommendations. Bipolar Ag/AgCl surface electrodes will be positioned parallel to muscle fiber orientation with an inter-electrode distance of 20 mm. Skin preparation will include shaving, when necessary, gentle abrasion, and cleaning with alcohol to reduce impedance.

Force measurements and sEMG signals will be recorded simultaneously and synchronized through the acquisition software. Raw signals will be visually inspected prior to analysis to identify artifacts and signal abnormalities.

Signal processing will include band-pass filtering, full-wave rectification, and frequency-domain analysis using Fast Fourier Transform (FFT) techniques. Spectral analyses will be performed using Hamming windows of 1024 samples with 50% overlap. Mean and median frequency parameters will be calculated from consecutive one-second epochs during the sustained contraction task.

Prior to analysis, all recordings will undergo visual inspection and quality-control procedures. Signal segments will be excluded if they exhibit evidence of electrode displacement, signal saturation, excessive baseline noise, movement artifacts, abrupt signal discontinuities, or other technical abnormalities that may compromise signal interpretation. When multiple epochs are available, only artifact-free segments meeting predefined quality criteria will be included in the final analysis.

To ensure reliability in the bedside hospital setting, all evaluators will undergo standardized training, and all procedures will follow predefined operating protocols. Electrode placement sites will be systematically documented to ensure consistent positioning across repeated measurements.

Safety Monitoring and Adverse Event Recording

All assessments will be performed only when participants are considered clinically stable by the attending medical team. Prior to each testing session, patients will be screened for contraindications, including acute clinical deterioration, uncontrolled pain, severe fatigue, hemodynamic instability, active infection requiring urgent intervention, or any condition that may compromise safe participation.

Adverse events occurring during or immediately after testing will be documented, including dizziness, excessive fatigue, pain exacerbation, musculoskeletal discomfort, cardiovascular symptoms, falls, or any unexpected clinical event. The severity, duration, and relationship to the assessment procedure will be recorded.

Testing will be immediately discontinued if participants report intolerable discomfort, request termination, exhibit signs of excessive fatigue, develop cardiovascular symptoms, or if the research team determines that continuation may compromise safety. Participant safety will always take precedence over protocol completion.

Serum biomarkers—Basic Panel

Laboratory assessments will be performed at hospital admission and discharge. In cases where daily blood tests are required for clinical reasons, these additional results will be incorporated into the longitudinal analysis.

The following parameters will be collected: albumin, prealbumin, C-reactive protein (CRP), creatinine, complete blood count, lipid profile, and glucose. From these values, several derived indices will be calculated, including the Prognostic Nutritional Index (PNI) [52,53,54,55,56], the neutrophil-to-lymphocyte ratio (NLR) [57,58,59,60], the CRP/albumin ratio [61,62], and the CRP/prealbumin ratio [63], as integrated markers of inflammatory, nutritional, and catabolic status.

Additionally, Growth Differentiation Factor 15 (GDF-15) will be determined as an exploratory biomarker of cancer-related cachexia. GDF-15 has been associated with anorexia, systemic catabolism, involuntary weight loss, and adverse clinical outcomes in oncology populations, making it a promising candidate marker for identifying patients at risk of accelerated muscle deterioration.

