### 2.2. Secondary Objectives

Secondary objectives include the characterization of daily trajectories of muscle function, neuromuscular fatigue, body composition, and biomarker profiles during hospitalization.

To describe in-hospital trajectories of muscle function through daily assessment of neuromuscular fatigue using sEMG (MDF, MNF, fatigue slope, and, when applicable, time to failure).To determine admission-to-discharge changes in phase angle derived from bioimpedance and in serum indices related to inflammation and nutritional status (Prognostic Nutritional Index, Neutrophil-to-Lymphocyte Ratio, CRP/albumin ratio, CRP/prealbumin ratio).To evaluate associations between muscle deterioration and patient-reported outcomes related to sleep quality, quality of life and symptoms, including the SARC-F, EORTC QLQ-C30, and PSQI scales.

An additional exploratory objective is to identify candidate clinical, functional, electrophysiological, and biochemical variables associated with greater muscle deterioration during hospitalization, with the aim of informing future hypothesis-driven studies.

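### The numeric failure limit for time to failure is tied to 65% MVC, although the sEMG contraction may be done at 50% MVC

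*Protocol article*

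**What the plan says.** All of the relevant rules but two are in the protocol article, section 3.4, under Surface Electromyography.

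- **Lower limb.** The contraction at 65% MVC runs to "muscle failure, defined as the inability to maintain the target intensity (±5–10%) for more than 3–5 consecutive seconds". This ties failure to the target.
- **Upper trapezius.** "This will be followed by an isometric contraction at 65% of MVC using biofeedback via a portable dynamometer until muscle failure". No numeric definition of failure is attached.
- **Step-down.** "Reduction to 50% MVC will only be considered when participants are unable to safely maintain the target force level during familiarization, report excessive fatigue"; pain, discomfort and a safety judgement by the research team are further grounds. A later sentence adds that, for patients with clinical limitations, "the protocol may be adjusted to 50% MVC to ensure safety without compromising the acquisition of fatigue parameters".
- **Recording.** "The contraction intensity selected and the reason for any modification will be documented for each assessment".
- **Time to failure.** The index is first "defined as the moment when the participant was no longer able to maintain the target force level". The numeric criterion follows in the same item: "failure was considered when force decreased persistently by more than 5–10% below 65% of MVC during the isometric contraction".

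Section 2.2 lists the sEMG measures as "MDF, MNF, fatigue slope, and, when applicable, time to failure". Section 3.9 says that exploratory analyses will take contraction intensity into account and will stratify by it where numbers allow. It plans no direct comparison between intensities.

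**The concern.** Two contraction levels are permitted, but the numeric failure limit is written for one of them. At 65% MVC the target-based wording and the 65%-based wording give the same lower limit, so the problem stays hidden. At 50% they separate: one gives a measurable time, and the other places the whole contraction below the limit. The article also says that the 50% option leaves the fatigue parameters obtainable, which is not true of time to failure if the numeric clause is applied as it stands.

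Consistent scoring is at stake. Two evaluators could each follow the document and record different values for the same 50% test. Those tests are not a random subset. The grounds for stepping down are inability to hold 65%, fatigue, pain, discomfort or a safety concern, so any inconsistency falls on the sessions in which muscle function is poorest. Accounting for intensity in the analysis does not change the failure limit, and it does not show which limit was used for a given test.

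**Working it through.** The plan gives no figure of its own to reproduce. The check compares the stated limit with the permitted target.

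**Inputs** (all from section 3.4, Surface Electromyography): standard target 65% MVC; permitted reduced target 50% MVC; allowed drop 5–10%; reference level in the numeric criterion 65% MVC; reference level in the lower-limb definition and in the opening clause of the time-to-failure item, the target.

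The article does not say whether the 5–10% is relative or in points of MVC, so both are computed.

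**Formulas.** Relative: limit = reference × (1 − drop). Points: limit = reference − drop.

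| Reference level | Reading | 5% drop | 10% drop |
|---|---|---|---|
| 65% MVC (numeric criterion) | relative | 65 × 0.95 = 61.75 | 65 × 0.90 = 58.5 |
| 65% MVC (numeric criterion) | points | 65 − 5 = 60 | 65 − 10 = 55 |
| 50% MVC (target-based wording) | relative | 50 × 0.95 = 47.5 | 50 × 0.90 = 45 |
| 50% MVC (target-based wording) | points | 50 − 5 = 45 | 50 − 10 = 40 |

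**A perfect hold at 50% MVC**

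- Distance from 65%: 65 − 50 = 15 points; 15 / 65 = 23.1%. The allowed drop is 5–10%.
- Against the 65%-based limit, it is under by 61.75 − 50 = 11.75, 58.5 − 50 = 8.5, 60 − 50 = 10 or 55 − 50 = 5 points. It is below the limit on all four readings, including the most lenient (55% MVC).
- Against the target-based limit, it is above by 50 − 47.5 = 2.5, 50 − 45 = 5 (relative, 10%), 50 − 45 = 5 (points, 5) or 50 − 40 = 10 points. Time to failure can then be measured.

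**Resulting scores for one 50% test**

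1. Numeric criterion as a fixed threshold: the force is under the limit from the first second, so the time is zero.
2. Numeric criterion as requiring a fall through the limit: force that never stood above the limit cannot fall through it, so there is no value.
3. Target-based wording: a real time, ending when force falls below 47.5–45% MVC (relative) or 45–40% MVC (points).

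For the trapezius, the target-based opening clause still applies, but the 65%-based criterion is the only numeric rule not placed under the lower-limb protocol.

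**The case against.** The strongest reply is that the intent is clear. The time-to-failure item opens by defining failure against the target, the lower-limb protocol does the same, and the article says that the 50% option does not compromise the fatigue parameters. On that view the 65% figure is a leftover that restates the rule for the standard intensity. The criterion also speaks of force that has decreased persistently, and a steady hold on a 50% target has not decreased. Evaluators are to be trained and to work from operating protocols that an article need not reproduce. The index is exploratory and conditional, step-down is an exception, and force is recorded together with sEMG, so scores can be revisited.

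Most of this stands, and it limits the point. A reader might infer that 50% tests have no valid time to failure, or that the daily trajectory will in practice rest only on the stronger sessions. The documents do not support either inference. Target-based definitions that work at 50% are in the text, nothing shows that evaluators would score a 50% test as failed at onset, and the article gives no step-down rate from which to count affected tests.

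The reply does not remove the conflict. Reading the criterion as a rule about decline avoids the zero but still gives no usable limit for a 50% test. Likely intent is not a scoring rule when the one number given with the index contradicts it. This is not detail left to a fuller document, because the article itself states both rules.

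**Conclusion.** The numeric criterion is wrong as written for a test condition that the protocol permits, and it conflicts with the target-based wording in the same section. That a 50% hold lies 5 to 11.75 points under the stated limit needs no assumption beyond the article's own numbers, and it holds on either reading of the 5–10%.

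The consequence is ambiguity rather than certain loss: a 50% test may be scored as zero, as missing or as a real time. How many tests this touches cannot be stated.

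The reach is narrow. Only time to failure is scored directly by this limit. The median-frequency slope and the final/initial RMS ratio can still be computed at 50%, although the point at which the contraction is taken to end could depend on the rule used. The primary endpoint, change in dominant-hand handgrip strength, and the sample size are unaffected. This is a minor correction worth making before time to failure is analysed.

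**What to change.** In section 3.4, in the time-to-failure item, replace *65% of MVC* with *the target intensity used in that test (65% or 50% MVC)*. State that the target-based definition now under the lower-limb protocol applies to both the quadriceps and the upper trapezius. Rescore any 50% tests already done from the stored force traces.

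The cost is one phrase and one sentence. No new visit, data field or patient is needed, because the intensity of each assessment is already documented and force is recorded in synchrony with sEMG. Rescoring assumes that the traces are kept and that the contraction was not ended early on the 65%-based rule.

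### The sEMG spectral settings conflict with one another: rectification is listed ahead of the FFT, the upper cut-off equals Nyquist, and the window does not fit the epoch

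*Protocol article*

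**What the plan says.** All the settings are in section 3.4 (Instruments) of the protocol article.

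- **Surface Electromyography (sEMG):** "Signals were acquired at a sampling frequency of 1000 Hz", and "A band-pass filter between 10 and 500 Hz was applied to remove low-frequency components and high-frequency noise". A 50 Hz notch is added. In the time domain, RMS is computed and normalised to the maximal contraction. In the frequency domain, MDF and MNF come from an FFT, "applying consistent analysis windows throughout the signal to ensure spectral stability". The fatigue indices include this one: "Temporal slope of MDF during sustained contraction".
- **sEMG Acquisition and Signal Processing Procedures:** "Signal processing will include band-pass filtering, full-wave rectification, and frequency-domain analysis using Fast Fourier Transform (FFT) techniques". Then: "Spectral analyses will be performed using Hamming windows of 1024 samples with 50% overlap". Then: "Mean and median frequency parameters will be calculated from consecutive one-second epochs during the sustained contraction task".

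Section 2.2 names MDF, MNF and the fatigue slope in its first listed secondary objective. Section 3.3.2 classes all sEMG parameters as secondary/exploratory.

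The article does not say that the spectrum is taken from the unrectified signal, that rectification serves amplitude only, that epochs are zero-padded, or that 500 Hz is an analogue or device setting.

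**The concern.** The article states specific values, and those values can be checked against one another. Three of them do not fit.

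(a) Full-wave rectification stands between the band-pass and the FFT and is given no other purpose. Rectification is non-linear: it adds a DC term and components at sum and difference frequencies. The spectrum of a rectified trace is therefore not the EMG spectrum, and its median and mean are not MDF and MNF as usually understood.

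(b) The upper filter edge sits exactly at half the sampling rate, so a digital filter with that edge cannot do what the text says it is for.

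(c) The spectral window is longer than the epoch it is meant to analyse, and overlapping windows are a different rule from back-to-back epochs.

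At stake is whether two analysts working from this text would obtain the same MDF, MNF and MDF slope. These feed the daily mixed models and the association models of section 3.9.

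**Working it through.** There is no figure of the plan's own to reproduce. The check uses the stated settings, then a simulation for size.

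**Inputs from section 3.4:** sampling rate fs = 1000 Hz; band-pass 10–500 Hz; Hamming window of 1024 samples; overlap 50%; epoch 1 s.

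**Cut-off.** Nyquist = fs/2 = 1000/2 = 500 Hz, equal to the stated upper edge. A digital Butterworth design with edges 10 and 500 Hz at 1000 Hz is rejected, because critical frequencies must lie strictly below fs/2. Designs with upper edges of 499, 450 and 400 Hz are accepted.

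**Window against epoch.**
- Window duration = 1024/1000 = 1.024 s. One epoch holds 1000 samples, so the window is 24 samples too long.
- Step at 50% overlap = 512/1000 = 0.512 s, not 1 s.
- Points in a 60 s contraction, back-to-back epochs: 60000/1000 = 60.
- Points in 60 s, overlapping windows: floor((60000 − 1024)/512) + 1 = 115 + 1 = 116.
- A standard Welch routine given a 1000-sample epoch shortens the window to 1000 with a warning. It fails if a 1024-point window is forced.

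**Rectification (simulation; the spectra are assumptions, not from the documents).** 60 s of Gaussian noise was shaped to the power spectrum f²·fh⁴/[(f² + fl²)(f² + fh²)²], with (fl, fh) = (60, 120), (50, 95) and (40, 75) Hz for fresh, mid and fatigued states. A 10 Hz high-pass and a 50 Hz notch were applied. The table uses 1000-sample Hamming epochs zero-padded to 1024; values are in Hz.

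| State | MDF unrectified | MDF rectified, mean removed | Ratio | MDF rectified, DC kept | MNF unrectified | MNF rectified, mean removed | MNF rectified, DC kept |
|---|---|---|---|---|---|---|---|
| Fresh | 98.6 | 146.6 | 1.49 | 0 | 119.1 | 165.6 | 41.7 |
| Mid | 80.6 | 118.3 | 1.47 | 0 | 97.9 | 139.8 | 35.0 |
| Fatigued | 64.2 | 97.9 | 1.52 | 0 | 79.4 | 116.9 | 29.4 |

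- Absolute fall in MDF, fresh to fatigued: 98.6 − 64.2 = 34.4 Hz unrectified; 146.6 − 97.9 = 48.7 Hz rectified with the mean removed (48.7/34.4 = 1.42 times).
- Proportional fall: 34.4/98.6 = 35% against 48.7/146.6 = 33%.
- A second simulation used four fatigue levels and counted only frequencies from 10 Hz up. MDF went from 93.8/80.1/64.5/48.8 to 148.4/127.0/105.5/83.0 Hz, ratios 1.58 to 1.70. The proportional fall was 48% unrectified and 44% rectified. With DC kept, MDF was 0.98 Hz at every level.

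The collapse with DC kept follows from the algebra. For a zero-mean Gaussian signal with standard deviation σ, the mean of |x| is σ√(2/π). The DC share of total power is then 2/π ≈ 0.64. More than half the power lies at zero frequency, so the median falls there. One frequency bin is 1000/1024 = 0.98 Hz, which is why the result is reported as 0 or about 1 Hz.

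**Effect of the window rule alone.** Mean unrectified MDF under three readings (1000 samples zero-padded; 1024 sliding; 512 sliding) was 98.6/98.5/98.3 fresh, 80.6/79.2/79.8 mid and 64.2/63.9/64.6 fatigued. The largest difference is 80.6 − 79.2 = 1.4 Hz.

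**The case against.** The strongest reply concerns rectification. The sentence says what processing will include; it does not say that one step feeds the next. The article elsewhere separates RMS in the time domain from MDF and MNF in the frequency domain and mentions no rectification there. An unordered list covering both kinds of analysis is a possible reading. Section 3.4 also refers to predefined operating protocols, which are not shown and may settle the order. This stands in part: the article does not prove that the FFT will be run on a rectified trace. But RMS needs no rectification, since squaring already removes the sign, so rectification has no stated use other than the step listed after it. The text leaves the choice open.

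A reader might go further and infer that the spectral outcomes are invalid or that the fatigue slope would be zero. The documents do not support that. A zero slope needs both rectification before the FFT and a retained DC term, and the article states neither a retained DC term nor mean removal. With the mean removed, the level and absolute slope are inflated, but the direction is preserved and the proportional decline nearly so.

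A reader might also infer that the pipeline cannot be run. A digital 10–500 Hz design is indeed rejected, and a 1024-sample window does not fit a 1000-sample epoch. But the article does not say that the band is a digital design rather than a device setting, and software may shorten the window unprompted. The cut-off conflict means no effective digital low-pass, with the high-pass and notch still in place. The window conflict moves mean MDF by about 1.5 Hz or less, and no bias in the slope was shown.

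**Conclusion.** The concern holds as an inconsistency in stated settings, of moderate severity. It is not a detail left to a fuller document: the values are given, and they conflict.

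The rectification wording carries the weight. If followed in the listed order, it raises MDF about 1.5-fold with the mean removed (up to 1.7-fold when frequencies below 10 Hz are also dropped), or pins it near 0–1 Hz with DC kept. These sizes rest on assumed Gaussian signals and assumed spectral shapes, so they show direction and order of magnitude only. The cut-off and window conflicts are certain by arithmetic but have little effect on mean MDF.

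The reach is limited to MDF, MNF and the MDF slope, together with the exploratory models that use them. The primary endpoint, change in dominant-hand handgrip strength, and its sample size are untouched.

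**What to change.** Amend the sEMG text in section 3.4 in three places, before any spectral outcome is analysed:

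1. State that MDF and MNF are computed on the band-passed, unrectified, mean-removed signal, and that rectification is used only for amplitude envelopes, if at all.
2. Set the upper cut-off below 500 Hz, or state that no digital low-pass is applied.
3. Fix one window rule for all slopes: either consecutive 1000-sample epochs zero-padded to 1024, or 1.024 s windows with 50% overlap.

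The cost is protocol wording and a change to the processing script. No new measurements are needed, because stored raw signals can be reprocessed. Making the change before analysis also avoids choosing the pipeline after the results are seen.
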